**1.5. Potential effect of IPTi on clinical immunity**

A potential negative influence of IPTi on clinical immunity to malaria, which is normally acquired naturally as the consequence of repeated *P. falciparum* infections, remains an import question. This might lead to a rebound effect on malarial morbidity with an increased incidence of mild or severe malaria in the second year of life, despite the beneficial effect of IPTi on the burden of disease during the first 12 months. Protective immunity has been shown to be mediated, at least partly, by the acquisition of agglutinating antibodies against parasite-encoded, variant-specific antigens on the surface of infected red blood cells, the variant surface antigens.33,34 Protection is related to the acquisition of a broad repertoire of anti-VSA antibodies, and antibodies against a specific subset of parasite antigens that are particularly well expressed during infections in young children have been shown to be related to protection from severe disease during the first few years of life.35-37 Studies have further shown that asymptomatic low-density parasitaemia in children in itself is linked to a lower incidence of uncomplicated malaria.38 Together, these findings point to the importance of asymptomatic,low-grade parasitaemia in the induction of protective anti-VSA antibodies during infancy, particularly against severe forms of disease; a protection that may be disrupted by a repeated clearance of parasitaemia by presumptive intermittent treatment. Thus, it is important to assess the interaction between IPTi and the development of clinical immunity in children.

**1.6 The influence of G6PD deficiency and human haemoglobinopathies**

Glucose-6-phosphate (G6PD) deficiency and human haemoglobinopathies, such as sickle cell trait and alpha-thalasseamia are (important) inherited genetic factors, which may influence the outcome of IPTi43,44. G6PD-deficient red blood cells are more susceptible to oxidative stress, and haemolytic anaemia more prone to develop in G6PD-deficient patients receiving antimalarial drugs such as SP and Lapdap45. By monitoring the prevalence of G6PD deficiency in the study population, it will be possible to predict the risk of haemolytic anaemia among the study participants treated with these drugs, and further to adjust for the effect of G6PD deficiency when analysing the effect of different IPTi drugs on the prevalence of anaemia. Furthermore, by testing for these genetic factors, which have been associated with innate resistance to malaria, it will be possible to adjust for their influence when assessing the possible influence of different IPTi drugs on malaria morbidity and acquired immunity.

1. **Objectives**

**2.1 Co-primary objectives**

This study has four main objectives

- Identification of a drug that could be used safely and effectively for IPTi instead of SP in areas, such as north eastern Tanzania, where there are high levels of resistance to SP and amodiaquine.
- Determination of whether a short acting antimalarial drug (Lapdap) is as effective as a long acting drug (mefloquine) when used for IPTi.
- Investigation of the effect of the intensity of transmission on the requirements for a long or short acting drug for IPTi.
- Assessment of the effect of IPTi on the development of clinical immunity in children in low and high transmission areas.

2.2 Secondary objective

- To determine whether IPTi through the EPI interacts with the immune response to routine immunisations
- Assessment of the effect of G6PD deficiency and haemoglobinopathies on the outcome of IPTi.

**3. Study area**

The study will be conducted in two sites in Tanzania: (1) a low/moderate transmission area in South Pare district ; (2) a high transmission area in western Usambara district A

**Figure1: Parasite prevalence in the Kilimanjaro region**

[figure not shown]

Source: Drakeley C, Reyburn et al. MIM conference abstract no. 318, Arusha, Tanzania

malariometric survey in 2002 showed significant variation in the prevalence of malaria parasitaemia in <5 year old children at different levels of altitudes within and between the

districts (Figure 2). The survey was conducted in four groups of villages: Rombo (purple), South Pare (pink), Western Usamabara (yellow) and Eastern Usambara (grey). The relationship between the mean altitude of the village and the prevalence of parasitaemia is shown in the graph (insert). The mean altitude of villages within in each group ranged from 200 to 1800 meters. The prevalence of malaria parasite in 0-4 year old children ranged from 20% to 55% in the lowlands (<750m) and from 1% to 20% at 1000-1500m altitude. The malaria transmission pressure in lowland villages in the South Pare district is low/moderate. The prevalence of malaria parasitaemia was 30% in 1-4 year-old children and 4% in <1 year-old infants. The prevalence of parasitaemia was higher in Western Usambara villages (52% in 1-4 year-old children and 20% in <1 year-old infants).

The advantages of the study site for the proposed trial are:-

1. Levels of resistance to SP and amodiaquine are high and so investigation of alternative drugs that could be used for IPTi is needed urgently and can be justified ethically.
2. A wide range of levels of malaria transmission are found over a small area in a homogeneous population.
3. The epidemiology of malaria in the study area has recently been carefully defined.

Although detailed epidemiological studies have recently been undertaken in the study area, it will be necessary to confirm that major differences persist between highland and lowland sites during the period of the trial. We have considered the possibility of making direct measurements of EIR but this is difficult and expensive in low transmission areas because of the paucity of anopheline mosquitoes and the low sporozoite rate. In a recent study in Hai district, Tanzania, 2198 anopheline mosquitoes were collected over a period of 12 months and only 8 mosquito were infected giving an EIR with very wide confidence limits. Instead of EIR estimates, we will rely upon the prevalence of infection in nine month old infants in the placebo groups to estimate the force of infection in the two sites.

The number of infants receiving DPT1 (the expected number of infants that can be enrolled in a year) and laboratory facilities available in the health facilities serving the populations of South Pare and Western Usambara are shown in Tables 3 and 4

**Table3. Infant population and infrastructure of health facilities in South Pare**

| Name of health facility | Number of infants receiving DPT1 in 2002 | OPD cases in children <5 years-old in 2002 -  total | OPD cases in children <5 years-old in 2002 -  malaria | Laboratory facility | Power supply |
| --- | --- | --- | --- | --- | --- |
| Ndungo | 437 | 4025 | 1256 | Microscopy | electricity |
| Kisuwani | 273 | 3284 | 1291 | None | Kerosene |
| Kiturio | 196 | 5212 | 2135 | Microscope | Electricity |
| Bandera | 58 | 1821 | 556 | Microscope | Electricity |
| Gonja | 230 | 2615 | 1086 | Microscope | Electricity |
| Mpirani | 122 | 314 | 183 | Microscope | Electricity |
| Same | 638 | NA | NA | Microscope | Electricity |
| Mbono | 97 | 1030 | 384 | None | Kerosene |
| Vutima | 151 | 100 | 36 | None | Kerosene |
| Vumari | 72 | 1232 | 408 | None | Kerosene |

**Table4: Infant population and infrastructure of health facilities in Western Usambara**

| Name of health facility | Number of infants receiving DPT1 in 2002 | OPD cases in children <5 years-old in 2002 -  total | OPD cases in children <5 years-old in 2002 -  malaria | Laboratory facility | Power supply |
| --- | --- | --- | --- | --- | --- |
| Mbaramo | 312 | 3036 | 1047 | None | Kerosene |
| Mlalo | 601 | 8268 | 5877 | Microscope | Electricity |
| Kangagai | 141 | 1692 | 828 | Microscope | Electricity |
| Ngwelo | 260 | 1671 | 684 | None | Kerosene |
| Mnazi | 381 | 3646 | 1773 | Microscope | Kerosene |
| Kivingo | 94 | 1562 | 1022 | None | Kerosene |
| Mng’aro | 185 | 1755 | 1527 | None | Kerosene |

respectively. The study will be conducted in five health facilities in the South Pare district (Ndungo, Kisiwani, Gonja, Mpirani, Same) and in five in Western Usambara district (Mbaramo, Mlalo, Kangagai, Ngwelo, Mnazi). These health facilities were selected on the basis of the number of infants needed for the study (see below) and logistical feasibility.

**3.1. Change of study site**

A site visit by the principal investigators ([name], [name], [name]) to the proposed study site in June 2004 showed that two health facilities (Mlalo and Ngwelo) and their catchment areas are situated at an altitude >800 meters and that malaria transmission would be medium/low in these two populations. Hence infants attending these two health facilities, cannot be included in this study because Western Usambara is the high malaria transmission site chosen to address the question on differences in the efficacy of IPTi between high and medium/low transmission areas. Restricting the enrolment of infants to the remaining three health facilities in the Western Usambara will reduce the number of eligible study infants substantially and it will not be possible to enrol the required number of infants (1280) in 12 to 15 months. Therefore, another high transmission site is needed.

The transmission of malaria in the Lwengera valley in Korogwe district is high. The prevalence of malaria parasitaemia in <5 year old children in this area was 50-60% during the baseline survey conducted in 2002. The PIs met the Korogwe District Medical Officer (DMO) and his colleagues and discussed the possibility of conducting the IPTi study in Lwengera valley. The DMO and his team are very cooperative and supportive of this move. The PIs visited the health facilities and the surrounding villages in Lwengera valley in Korgowe district on the 7th of June 2004 and assessed the appropriateness and feasibility of conducting the study in Lwengera valley. The health facilities serving the population of Lwengera valley and the number of infants that could be recruited for this study in a year are shown in Table 5.

As a result of those discussions, a request to move the study from Lushoto to Korogowe district has been submitted to the ethics committees in Tanzania and at the London School of Hygiene & Tropical Medicine.

Table 5. Number of infants receiving DPT2 in Lwengera valley health facilities, 2003

| Health Facilities | Number of infants that received DPT2 in 2003 |
| --- | --- |
| Korogwe hospital MCH  Majongo dispensary  St Raphael Hosptial  Lwengera dispensary  Magazini dispensary  Mnyuzi dispensary | 250  200  50  160  140  180 |
| Total | 980 |

**3.2 Addition of Hale Dispensary as study site in Lwengera Valley**

Hale Dispensary has not been included in the main IPTi study and is being used as the study site for the IPTi Efficacy studies (NIMR ref: NIMR/HQ/R.8a/Vol. IX/434).

**4. Study Methodology**

**4.1. Study design**

The overall study design is a randomised trial of four treatment regimes in two different transmission settings. The key steps and the arms of the study are shown in Figure 2. The four treatment regimes are as follows: (1) placebo, (2) mefloquine; (3) Lapdap; (4) SP. All medications will be given at the time of immunisation with DPT/polio 2, DPT/polio 3, and measles vaccines.

**4.2. Study population : inclusion/exclusion criteria**

The study population will be all infants attending EPI clinics at the 10 study health facilities (listed in section 3) for first vaccinations. Infants who live within the catchment area of the study health facility and are less than 3 months of age at the time of DPT and Polio 1 vaccination will be eligible for inclusion in the study. Infants having any of the following conditions will be excluded: (1) history of allergy to study drugs; (2) history of convulsions; (3) clinical features of severe malnutrition or chronic illness including infants with signs of AIDS [HIV prevalence in women of reproductive age in the study area was 11.5% in 1999]39 (4) plans to leave the study area before 12 months of age.(5) weighs <4.5 kgs (6) caretaker declines to give consent.

To assess how representative the sample population is of the population as a whole we will carry out a demographic survey of the study sites during the time of enrolment. This survey will take a random sample of dwellings within the study area and numerate the number of children under 5 years with an MCH/Vaccination card, numerate those eligible for enrolment into the study by age and those that have been enrolled into the study. Using census data we will extrapolate our results.

**Figure 2**. **Study design**

**Contact 0**: Infants attend EPI clinics for BCG and/or DPT & Polio1 vaccines

1. identification of eligible infants

2. provision of information about the study to the care takers

3. enrolment of eligible infants after obtaining informed consent

2 months

Approximate age

**Contact 1:** Infants return for DPT 2 and Polio 2 vaccines

1. random allocation to one of the study groups

2. administration of the first course of treatment

3. collection of blood samples for Hb and blood film and filter paper

4. appointment for contact 2 (DPT and polio 3)

Group 1

placebo

Group 2:

Mefloquine

Group 3:

Lapdap

Group 4:

SP

Passive surveillance at health facilities for side effects of drugs, clinical malaria, and anaemia until 24 months of age

**Contact 2**: Infants attend EPI clinic for DPT 3 & Polio 3 vaccines

1. completion of data forms and administration of the second course of allocated drug

2. appointment for contact 3 (measles vaccine)

**Contact 3**: Infants attend EPI clinic for measles vaccine

1. completion of data forms and administration of the third course of allocated drug
2. collection of blood samples for baseline measles serology
3. appointment for contact 4 (1 month after the date of contact 3)

**Contact 4**: (1 month after the date of contact 3)

Collection of blood samples for Hb, blood film, post vaccine measles serology, and anti-VSA antibody assay

1 months

3 months

9 months

10 months

**Contact 5**: (20% random sample)

Collection of blood sample for Hb and blood film

**Contact 6**: (20% random sample)

Collection of blood sample for Hb and blood film

**Contact 7**:

Collection of blood sample for Hb, blood film & antibody assay

11 months

12 months

18 months

**Contact 8:**

for Hb, blood film, & filter paper, and screening by Paracheck dipsticks for malaria parasites

Random allocation of treatment for malaria for those +ve for malaria parasites by dipstick

**Contact 9: (Blood film +ve at contact 8 only)**

Collection of blood sample for blood film and filter paper

**Contact 10: (Blood film +ve on contact 8 only)**

Collection of blood sample for blood film and filter paper

24 months

Post treat-ment day 14

Post treat-ment day 28

**4.3. Outcome measures**

*Primary outcome measures*

1. Incidence of clinical malaria: [(history of fever during previous 2 days or axillary temperature >37.5ºC) + parasitaemia of any density + absence of any other obvious causes of fever] during the period of 2-11 months of age

*Secondary outcome measure*

1. Mean Hb at 10-12 months of age (one month after the third course of IPTi)
2. Incidence of severe anaemia (Hb <7 g/dl) during the period of 2-11 months of age
3. Prevalence of parasitaemia at 10-12 months of age (one month after the third course of IPTi)
4. Incidence of clinical malaria [as defined above] during the period of 12-23 months of age.
5. Level and repertoires of plasma antibodies to *plasmodium falciparum* variant surface antigen (anti-VSA antibodies) at 10 and 18 months of age.
6. EPI serology
7. Prevalence of G6PD deficiency and human haemoglobinopathies.

**4.4. Sample size**

The number of infants per arm needed for a study with 80% power and 95% significance for the primary and secondary outcome measures in the low/moderate transmission site

(South Pare) is shown in Table 6a. The required sample size was calculated using STATA software and based on the following assumptions:

1. the incidence of clinical malaria and anaemia in the placebo group in this setting will be similar to that observed by Schellenberg et al in Ifakara, Tanzania in 1999-2000;13
2. The effect of IPTi with mefloquine on clinical malaria and anaemia is similar to that of IPTi with SP observed by Schellenberg et al.;13
3. The effect of IPTi with Lapdap on clinical malaria and anaemia will be 50% less than the effect of mefloquine because Lapdap has little or no chemoprophylactic effect;
4. The effect of IPTi with SP on clinical malaria and anaemia will be 50% less than the effect of mefloquine because the resistance to SP in this setting is expected to be 50%.

Low transmission site: For the comparison of the primary outcome measure, the highest number infants (551) needed is for the comparison of the incidence of malaria between placebo and Lapdap groups. Allowing for 10% loss to follow up, 610 infants per arm i.e. a total of 2440 infants would be needed for the study in the South Pare district (see table 6a).

This sample size will have the power (90%) to detect a difference of 0.5g/dl Hb or less between the mefloquine and Lapdap arms, and also to detect a difference of 0.5g/dl between all treatment arms and placebo.

**Table 6a:** Estimates of the incidence or prevalence of primary and secondary outcomes in the comparison groups and the sample sizes required for a study in South Para area (low/moderate transmission)

| Endpoints | Expected rate/prevalence | | | Sample size per arm needed for a study with 80% power and 95% significance | | |
| --- | --- | --- | --- | --- | --- | --- |
|  | Placebo group | MQ group | Lapdap and SP groups | Placebo versus  MQ group | Placebo versus Lapdap or SP group | MQ versus  Lapdap or SP group |
| **Primary**   1. Incidence of clinical malaria in infants   **Secondary**   1. Mean Hb at 10 months of age 2. Incidence of severe anaemia in infants 3. Prevalence of parasite at 10 months of age 4. Risk of clinical malaria at 12-23 months | 0.40/child/yra  9.5 gm/dlc  0.16/child/yra  30%c  0.40/childf | 0.20/child/yra  10.5 gm/dld  0.08/child/yra  15%e  0.56/childg | 0.30/child/yrb  10.0 gm/dlb  0.12/child/yrb  20% e  0.48/childh | 118  63  295  121  295 | **551**  252  1,377  294  628 | 393  252  984  908  636 |

aBased on estimates from Ifakara in 1999-2000 (Schellenberg et al) in the placebo and SP groups.

bAssumes that the effect of Lapdap on clinical malaria and anaemia will be 50% less than MQ because Lapdap has very little or no chemoprophylactic effect and that the effect of SP will also be 50% less than MQ because the resistance to SP in this area is 50%.

cBased on estimates from surveys done in Kilimanjro region in 2001-2002 (MRC-1 and Hai projects - unpublished).

d50% reduction in the incidence of severe anaemia was based on the observation in Ifakara in 1999 and it is assumed that this would increase the mean Hb at 10 months of age by 1 gm/dl.

e Assumes that the reduction in the prevalence of parasitaemia at 10 months of age would be similar to the reduction in the incidence of clinical malaria.

fAssumes that the incidence of malaria in the second year of life would be similar to the first year and that 25% of these infection will be severe.

gAssumes that incidence of malaria in the MQ group will increase by 40% in the second year of life

hAssumes that the incidence of malaria in the Lapdap and SP groups will increase by 20% in the second year of life.

The number of infants per arm needed for a study with 80% power and 95% significance for the primary and secondary outcome measures in the high transmission site (Western Usambara) is shown in Table 6b. For the comparison of the primary outcome measures, the highest number infants (291) needed was for the comparison of incidence of malaria between placebo and Lapdap groups. Allowing for 10% loss to follow up, 320 infants per arm ie. a total of 1280 infants would be needed for the study in the Western Usambara district.

For the comparison of the incidence of clinical malaria in the second year of life (rebound effect) the data from the two sites has to be combined. This combined population would have adequate power to compare the incidence between the placebo group and the mefloquine group. However, this sample size may not be adequate for comparing between the placebo and Lapdap group unless the rebound effect is as high as that in the mefloquine group.

**Table 6b:** Estimates of the incidence or prevalence of primary and secondary outcomes in the comparison groups and the sample sizes required for a study in Western Usambara area (high transmission)

| Endpoints | Expected rate/prevalence | | | Sample size per arm needed for a study with 80% power and 95% significance | | |
| --- | --- | --- | --- | --- | --- | --- |
|  | Placebo group | MQ group | Lapdap and SP groups | Placebo versus  MQ group | Placebo versus  Lapdap or SP group | MQ versus  Lapdap or SP group |
| **Primary**   1. Incidence of clinical malaria in infants   **Secondary**   1. Mean Hb at 10 months of age 2. Incidence of severe anaemia in infants 3. Prevalence of parasite at 10 months of age 4. risk of clinical malaria at 12-23 months | 0.62/child/yra  9 gm/dlc  0.39/child/yra  40%c  0.62/childf | 0.30/child/yra  10 gm/dl d  0.20/child/yra  20% e  0.86/childg | 0.45/child/yrb  9.5 gm/dlb  0.30/child/yrb  30% e  0.74/childh | 71  63  129  81  59 | **291**  252  670  357  252 | 262  252  393  294  190 |

aBased on estimates from Ifakara in 1995 (Menendez et al) in placebo and Deltaprim groups

bAssumes that the effect of Lapdap on clinical malaria and anaemia will be50% less than MQ because Lapdap has very little or no chemoprophylactic effect and that the effect of SP will also be 50% less than MQ because the resistance to SP in this area is 50%.

cBased on estimates from surveys done in Kilimanjro region in 2001-2002 (MRC-1; unpublished).

d50% reduction in the incidence of severe anaemia was based on the observation in Ifakara in 1999 and it is assumed that this would increase the mean Hb at 10 months of age by about 1 gm/dl.

e Assumes that the reduction in the prevalence of parasitaemia at 10 months of age would be similar to the reduction in the incidence of clinical malaria.

fAssumes that the incidence of malaria in the second year of life would be similar to the first year and that 20% of these infection will be severe.

gAssumes that incidence of malaria in the MQ group will increase by 40% in the second year of life

hAssumes that the incidence of malaria in the Lapdap and SP groups will increase by 20% in the second year of life.

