There will be two comparisons which are relevant with respect to multiple comparison, Lapdap vs Placebo and SP vs Placebo, and Mefloquine vs placebo will be the primary comparison. As we expect the effects of the two drugs to be similar, it would not be appropriate to power the trial on the Lapdap vs SP comparison. If we make two comparisons at the .025 level of significance then, under the null hypothesis, there is a .05 probability that one will be significant by chance. However we argue it would be appropriate to conduct one-sided tests, on the basis that there is no mechanism by which those given the active drug would have more malaria in the first year than those who do not.

We considered the possibility of powering the study at the 0.025 significance level rather than 0.05 level to allow for an excess of malaria in the first year of life among those on the active drugs in order to get over issue of the multiple comparisons. This would require increasing the sample size by 20%. This would mean increasing the number of infants in the low transmission are from 2200 to 2600 and in the high transmission areas from 1200 to 1440. This would require prolonging the study by four months. Thus,

we have opted to keep the power of the study at 0.05 level for the following reasons: (1) an enhanced incidence of malaria during the first year of life while on an active drug is very unlikely and so we can use a one-sided test (2) enrolling an additional 640 infants would increase substantially the logistical complexity and cost of the study but the added value of this would be small.

A detailed analytical plan will be prepared and submitted to the DSMB before the study drug codes are broken.

1. **Dissemination of results**

The nature of the trial and its possible implications will be discussed with the national Malaria Control and EPI programmes before the start of the trial. On completion of the study, results will be presented to the communities where the trial was undertaken, to local health authorities and to the National Malaria Control programme as well as in the international scientific press.

1. **Ethical considerations**

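### Table 6a's 20% parasitaemia for Lapdap/SP does not follow its own footnote, which gives 22.5%; the two sample sizes that use it (294 and 908) therefore do not match the stated assumption

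*Protocol*

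**What the plan says.** Section 4.4 gives, for South Pare, "The number of infants per arm needed for a study with 80% power and 95% significance" (Table 6a). The row for parasite prevalence at 10 months has 30% on placebo, 15% on MQ and 20% on Lapdap/SP. The sizes per arm are 121 (placebo v MQ), 294 (placebo v Lapdap/SP) and 908 (MQ v Lapdap/SP).

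Footnote e is attached to both the 15% and the 20%. Its rule reads: "the reduction in the prevalence of parasitaemia at 10 months of age would be similar to the reduction in the incidence of clinical malaria". The incidences it points to are in the first row of the table: 0.40 on placebo, 0.20 on MQ and 0.30 on Lapdap/SP. They follow the third listed assumption, "The effect of IPTi with Lapdap on clinical malaria and anaemia will be 50% less than the effect of mefloquine", and the matching assumption for SP.

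Enrolment is set by the primary outcome: "the highest number infants (551) needed is for the comparison of the incidence of malaria between placebo and Lapdap groups". The text then inflates this figure for attrition ("Allowing for 10% loss to follow up") and concludes: "610 infants per arm i.e. a total of 2440 infants would be needed".

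**The concern.** One cell departs from the rule that its own footnote states, and two of the three sizes in the row depend on that cell. The placebo and MQ values are fixed at 30% and 15%, so a Lapdap/SP value that is too low widens the gap from placebo and narrows the gap from MQ. One size is therefore too small for the stated assumption and the other too large.

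A reader of the row would conclude that placebo v Lapdap/SP on parasitaemia has ample room within the planned size. The same reader would conclude that MQ v Lapdap/SP, at 908, is out of reach with 610 per arm. Neither conclusion follows from the assumption in the footnote. Parasitaemia is secondary outcome 3 in section 4.3, so what is at stake is how the protocol describes its capacity on that outcome, and not the size of the trial.

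**Working it through.** **Inputs.** From Table 6a: incidence 0.40, 0.20 and 0.30; prevalence 30%, 15% and 20%. From the text of section 4.4: 80% power, 95% significance, equal arms, 610 per arm, 10% loss. Evaluable per arm: 610 × 0.90 = 549.

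**Step 1: the rule applied to each cell.**

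| Cell | Fall in clinical malaria | Prevalence by the rule | Printed |
|---|---|---|---|
| 6a, MQ | 1 − 0.20/0.40 = 50% | 30% × 0.50 = 15% | 15% |
| 6a, Lapdap/SP | 1 − 0.30/0.40 = 25% | 30% × 0.75 = 22.5% | 20% (a 33.3% fall) |
| 6b, MQ | 1 − 0.30/0.62 = 51.6% | 40% × 0.484 = 19.4% | 20% |
| 6b, Lapdap/SP | 1 − 0.45/0.62 = 27.4% | 40% × 0.726 = 29.0% | 30% |

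Three of the four cells agree with the rule to within about one percentage point. The Lapdap/SP cell in Table 6a is 2.5 points off. The half-of-MQ pattern shows the same thing. In Table 6a the Lapdap/SP effect is exactly half the MQ effect for malaria (0.10 of 0.20), haemoglobin (0.5 of 1.0 g/dl) and severe anaemia (0.04 of 0.08). For parasitaemia it is 10 of 15 points, or two-thirds.

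**Step 2: reproduce the printed sizes.** The formula is the two-proportion one with pooled variance under the null, two-sided 5%, 80% power and no continuity correction:

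n = [1.960·√(2p̄(1−p̄)) + 0.842·√(p₁(1−p₁) + p₂(1−p₂))]² / (p₁−p₂)², with p̄ = (p₁+p₂)/2.

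- 30% v 15%: 120.5, so 121 (printed 121).
- 30% v 20%: (1.2002 + 0.5119)² / 0.10² = 293.2, so 294 (printed 294).
- 15% v 20%: (1.0532 + 0.4513)² / 0.05² = 905.4, so 906 (printed 908).

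The same formula gives 82, 356 and 294 for the parasitaemia row of Table 6b (printed 81, 357 and 294). One-sided sizes for the Table 6a row would be 95, 231 and 714, and continuity-corrected sizes 134, 313 and 945. Neither set matches. The table is therefore two-sided and uncorrected, and 294 and 908 were calculated from 20%.

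**Step 3: the same formula at 22.5%.**

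- 30% v 22.5%: (1.2196 + 0.5218)² / 0.075² = 539.1, so 540 per arm (printed 294; ratio 1.84).
- 15% v 22.5%: (1.0819 + 0.4624)² / 0.075² = 423.97, so 424 per arm (printed 908; ratio 0.47).

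With a continuity correction these are 566 and 451.

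**Step 4: power at 549 per arm, two-sided 5%.** At the assumed 30% placebo prevalence:

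| Contrast | Lapdap/SP at 20% | Lapdap/SP at 22.5% |
|---|---|---|
| Placebo v Lapdap/SP | 97% | 81% |
| MQ v Lapdap/SP | 59% | 89% |

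Section 3 reports parasitaemia in lowland South Pare villages of 30% at 1–4 years and 4% under one year. Keeping the rule (MQ half, Lapdap/SP three-quarters of placebo) and varying the placebo prevalence:

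| Placebo prevalence | Placebo v Lapdap/SP | MQ v Lapdap/SP |
|---|---|---|
| 30% | 81% | 89% |
| 25% | 71% | 81% |
| 20% | 59% | 71% |
| 10% | 31% | 40% |
| 4% | 14% | 18% |

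**The case against.** **The footnote says similar, not equal.** Table 6b also departs slightly from equality, and every prevalence in both tables is a multiple of 5%, so 20% may be 22.5% rounded. That could explain how the cell arose. It does not excuse it, because the rounding changes one size by a factor of 1.84 and the other by a factor of 0.47. It does mean that 22.5% is not the only acceptable entry: 20% could stand with a reason of its own, which the protocol does not give.

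**The sizes are not miscalculated.** A reader might infer that 294 and 908 are arithmetic slips. They are not; both follow from the printed 20%.

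**Nothing in the design depends on this row.** This stands. The 551 evaluable and 610 enrolled per arm come from the primary outcome, and the MQ v Lapdap/SP size on that outcome (393) is unaffected. Table 6a also prints 1,377 and 984 for severe anaemia, both above 610, and the protocol leaves them there. It nowhere says that MQ v Lapdap/SP on parasitaemia is underpowered; a reader would infer that from 908.

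**Once corrected, is MQ v Lapdap/SP simply adequately powered?** A reader might infer this from 424 against 549. The documents do not support it without a condition. The 89% holds at 30% placebo prevalence, which equals the section 3 figure for children aged 1–4 years; the figure there for infants under one year is 4%. Footnote c cites unpublished regional surveys for the 30%, so the prevalence at 10 months cannot be settled from the protocol.

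**The one-sided argument.** The data analysis section argues of first-year malaria that "so we can use a one-sided test". The parasitaemia row was not calculated that way, so this does not explain the printed figures.

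**Conclusion.** The inconsistency is real and confined to one input. Under footnote e and the table's own incidences, Lapdap/SP prevalence is 22.5%. Placebo v Lapdap/SP then needs 540 per arm (printed 294) and MQ v Lapdap/SP needs 424 (printed 908). These figures rest on 30% placebo prevalence, two-sided 5%, 80% power, equal arms and no continuity correction, the settings that reproduce the printed row to within two infants.

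If the 30% holds, about 549 evaluable infants per arm give about 89% power for MQ v Lapdap/SP and about 81% for placebo v Lapdap/SP. The second has almost no margin (540 of 549), and with a continuity correction (566) it falls slightly short. Both powers drop at lower prevalence. The cell error itself does not depend on the placebo prevalence, but the power figures do. Enrolment and the primary outcome are unaffected.

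**What to change.** In Table 6a, either:

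- replace 20% by 22.5% for Lapdap/SP, 294 by 540 and 908 by 424; or
- keep 20%, 294 and 908, detach the cell from footnote e, and add a footnote that justifies a one-third reduction in parasitaemia beside a one-quarter reduction in clinical malaria.

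If the protocol comments on power for this outcome, it should say that the figures assume 30% placebo prevalence at 10 months, show how they fall at lower values, and set the 30% beside the 4% in section 3. The cost is three table cells or one footnote. No infants are added, and neither the design nor the primary analysis changes.
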